## Abstract

Acute upper gastrointestinal bleeding (AUGIB) is the commonest reason for hospitalization with hemorrhage in the UK and the leading indication for transfusion of red blood cells (RBCs). Observational studies suggest an association between more liberal RBC transfusion and adverse patient outcomes, and a recent randomised trial reported increased further bleeding and mortality with a liberal transfusion policy. TRIGGER (Transfusion in Gastrointestinal Bleeding) is a pragmatic, cluster randomized trial which aims to evaluate the feasibility and safety of implementing a restrictive versus liberal RBC transfusion policy in adult patients admitted with AUGIB. The trial will take place in 6 UK hospitals, and each centre will be randomly allocated to a transfusion policy. Clinicians throughout each hospital will manage all eligible patients according to the transfusion policy for the 6-month trial recruitment period. In the restrictive centers, patients become eligible for RBC transfusion when their hemoglobin is < 8 g/dL. In the liberal centers patients become eligible for transfusion once their hemoglobin is < 10 g/dL. All clinicians will have the discretion to transfuse outside of the policy but will be asked to document the reasons for doing so. Feasibility outcome measures include protocol adherence, recruitment rate, and evidence of selection bias. Clinical outcome measures include further bleeding, mortality, thromboembolic events, and infections. Quality of life will be measured using the EuroQol EQ-5D at day 28, and the costs associated with hospitalization for AUGIB in the UK will be estimated. Consent will be sought from participants or their representatives according to patient capacity for use of routine hospital data and day 28 follow up. The study has ethical approval for conduct in England and Scotland. Results will be analysed according to a pre-defined statistical analysis plan and disseminated in peer reviewed publications to relevant stakeholders. The results of this study will inform the feasibility and design of a phase III randomized trial.

ACUTE UPPER GASTROINTESTINAL bleeding (AUGIB) is the commonest reason for emergency hospital admission with a gastrointestinal disorder in the UK with an annual incidence of 50 to 150/100,000 adults [1]. It is the leading indication for red blood cell (RBC) transfusion, accounting for 14% of all RBCs transfused in England [2]. The purpose of RBC transfusion following AUGIB is to restore regional and global oxygen delivery. RBC transfusion is life-saving in exsanguinating patients, but most patients presenting with AUGIB do not have major hemorrhage, or features of hemodynamic compromise. In the 2007 UK audit of “AUGIB and the Use of Blood”, 62% of patients had no features of hemodynamic shock [3]. Most cases of AUGIB, regardless of etiology, will cease without the need for intervention. Many studies support this notion in that the rates of endoscopic intervention following AUGIB are in the order of 20-30% [4,5]. In most cases, RBCs are transfused because the hemoglobin (Hb) concentration has fallen below a threshold at which the physician believes the risks of anemia to outweigh the risks of transfusion. This perception of the appropriate threshold for transfusion is subjective but is likely to be influenced by multiple factors including the desire to have a “safe” Hb level in the event of re-bleeding, to reduce symptoms of anemia after bleeding has arrested, or by patient- and clinician-related factors. Hence, there is considerable practice variation with respect to RBC transfusion following AUGIB, with rates of transfusion ranging from 23% to 84% across 208 hospitals in the UK [3].

In other critically ill patient cohorts, a more liberal approach to transfusion has been associated with adverse clinical outcomes [6]. Two large observational studies have indicated a strong association between RBC transfusion after AUGIB and the risk of further bleeding, with a trend towards increased mortality, after adjustment for confounders [7,8]. These observations have now been supported by a recently published randomized trial in which rates of mortality and further bleeding were greater in the liberal transfusion arm [9]. Given the existing uncertainty and variation in transfusion practice for AUGIB and signals of harm associated with RBC transfusion, it is vital that the evidence base to inform the safe and effective use of RBCs is improved.

The purpose of this article is to describe the rationale and protocol for a cluster randomized controlled feasibility trial in the UK (TRIGGER—Transfusion in Gastrointestinal Bleeding) which aims to improve the evidence base for RBC transfusion in AUGIB. We also summarize the existing evidence and program of preliminary work, which has justified the need for and informed the design of the TRIGGER trial.

## Summary of Existing Evidence

### Evidence for Safe Transfusion Thresholds

Healthy humans can tolerate Hb levels as low as 5 g/dL without adverse consequences [10] and levels as low as 7 g/dL are safely tolerated in non-cardiac surgery, intensive care, and trauma patients [11]. However 13% of patients presenting with AUGIB in the UK have ischemic heart disease [3], raising concerns about the safe level of anemia in these patients. There are limited data indicating that subjects with coronary artery disease may be able to tolerate moderate normovolemic hemodilution well [12,13]. Lowering the Hb threshold for transfusion in patients undergoing coronary artery bypass surgery from 9 to 8g/dL [14], or from a hematocrit of 30% to 24%, did not result in higher morbidity or mortality [15]. The TRICC trial, a study comparing restrictive versus liberal RBC transfusion in intensive care patients, found no difference in mortality through use of a restrictive transfusion policy (Hb transfusion threshold < 7 g/dL) in a subgroup of 257 patients with known ischemic heart disease [16]. A systematic review of ten randomised controlled trials (RCTs) comparing clinical outcomes in restrictive versus liberal transfusion triggers concluded that a restrictive approach led to a 42% reduction in the probability of receiving transfusions with no effect on mortality, rates of cardiac events, morbidity, or length of hospital stay [11,17].

### Current Guidelines for RBC Transfusion in AUGIB

Current RBC transfusion practices in AUGIB are based upon consensus opinion. British Society of Gastroenterology guidelines recommend RBC transfusion when the Hb is ≤ 10 g/dL [18], but a more recent international guideline advocates transfusion when the Hb is ≤ 7g/dL [19]. For those with AUGIB secondary to portal hypertension, guidelines recommend maintaining the Hb around 8g/dL [20], but not higher. Although some consensus guidelines have advised against the use of a specific Hb level as an RBC transfusion trigger, several studies, mainly in critical care and surgery, have shown that clinicians attribute considerable importance to the Hb in making transfusion decisions [21]. This may be a reflection of the lack of physiological end points with sufficient sensitivity and specificity to guide transfusion decisions, especially outside a critical care setting.

### Sources of Harm and Cost of RBC Transfusion

Over the past decade there has been a marked change in critical care and surgical transfusion practice with an increased appreciation of the potentially harmful effects of allogeneic blood transfusion. Research in intensive care [22], cardiac surgery [23], and coronary care [24] suggest associations between blood transfusion and adverse patient outcomes, including death, even after adjustment for known confounders. Potential sources of harm from RBCs are poorly understood [25]. Some, such as transfusion-transmitted infection, transfusion-related acute lung injury, and hemolytic reactions are well defined but rare; transfusion-associated circulatory overload is unlikely to be rare but rather under-reported. Other possible mechanisms of harm include (1) adverse effects resulting from changes to RBCs that occur during blood storage [26]; (2) pro-inflammatory effects of blood transfusion [27] and; (3) transfusion of donor leukocytes, although the implementation of universal pre-storage leukocyte-reduction of blood components has reduced this risk [28].

Specific to AUGIB, the mechanism by which transfusion may be associated with further bleeding is unclear. In those patients with cirrhosis and portal hypertension who bleed from varices, excessive RBC transfusion is likely to worsen portal hypertension through volume overload, although it is possible that these effects may also occur with excessive fluid infusion per se as opposed to a unique effect of RBCs. However, this does not explain the mechanism in the majority of UK presentations with AUGIB in whom bleeding is non-variceal in origin (approx 90%). One postulated mechanism is that transfusion could counteract the splanchnic vasoconstrictive response after hypovolemic hemorrhage, resulting in a rebound increase in splanchnic blood pressure which could impair the ability to form clots [9]. It is unlikely that RBC transfusion would adversely impact upon the coagulation cascade to impair hemostasis. The mechanism of increased mortality with more liberal transfusion is most likely mediated through an excess of further bleeding, since this event is a strong and independent predictor of death [29].

## Preliminary Work to Inform the TRIGGER Trial

### The 2007 UK National Audit of AUGIB and the Use of Blood

This study provided detailed, “real-life” outcome data from 6750 patients with AUGIB admitted across 208 UK hospitals over a 2-month period [3,30]. The study highlighted areas of significant variation in transfusion practice and inappropriate use of RBCs; for example, 15% of all RBCs were transfused to patients with a Hb > 10 g/dL, who were hemodynamically stable. There was substantial clinical uncertainty in transfusion practice in patients presenting with a Hb between 8.1–10 g/dL. In this Hb range 51% of patients received transfusion and 49% did not. When patients were then stratified by the absence/presence of hemodynamic abnormality, the variability persisted. This range represents a genuine area of clinical uncertainty, practice variation, and potential equipoise in the RBC transfusion management of AUGIB.

### Outcomes Following Early RBC Transfusion for Acute Upper Gastrointestinal Bleeding

The relationship between early RBC transfusion, further bleeding, and mortality following AUGIB in 4,441 patients from the national audit data-set was examined. After adjusting for the clinical Rockall score [31] and initial Hb, early RBC transfusion was associated with a 2-fold increased risk of further bleeding (OR, 2.26; 95% CI 1.76-2.90) and a 28% increase in mortality (OR 1.28; 95% CI 0.94-1.74) [7]. Remarkably similar results were observed in a Canadian study of 1677 cases of AUGIB [8]. These studies suggest that many patients presenting with a Hb of > 8 g/dL following AUGIB may not benefit from transfusion, and could be harmed. Whilst these results do not prove a causal relationship, they indicate that a randomized comparison of restrictive and liberal transfusion policies in AUGIB is justified to confirm or refute the findings of these observational studies.

### A National Survey of Clinicians

A survey of UK clinicians was conducted with the aim of characterizing and understanding attitudes towards transfusion practice in patients with AUGIB [32]. Clinicians were asked to select a Hb threshold at which they would ordinarily transfuse RBCs in 6 realistic scenarios of AUGIB, and 815 clinicians responded. The most important patient characteristic raising the transfusion threshold was the presence of ischemic heart disease. The overall responses suggested belief that restrictive use of RBCs is appropriate, but were discordant with the observed practice in the national audit highlighting the discrepancy between theory and practice.

### A Systematic Review of Randomized Controlled Trials

A Cochrane systematic review was conducted in 2008 and updated in 2010 [33]. Only 3 small randomized controlled trials investigating differing RBC transfusion strategies in patients with AUGIB (total of 93 patients across 3 trials) were identified and all had methodological deficiencies. Whilst there was a trend towards increased mortality and further bleeding in the transfusion arms of the combined studies, the small number of participants and the large volume of missing data limited the generalizability of the findings. These data further support the need for a definitive randomized controlled trial to establish the risks and benefits of RBC transfusion in this population. The publication of a large trial subsequent to this Cochrane review will lead to an update of the review and a more precise estimate of treatment effects [9].

## Patients and Methods

### Trial Objectives

The objective of the TRIGGER trial is to evaluate the feasibility and safety of implementing a restrictive versus a liberal RBC transfusion policy in adult patients admitted with AUGIB, in order to inform the design of a definitive phase III trial.

### Design and Setting

TRIGGER is a pragmatic, cluster randomized feasibility trial comparing 2 different RBC transfusion strategies in patients admitted with AUGIB. Each participating center will be randomly allocated to one of 2 transfusion policies, and all eligible patients in a centre will be treated according to the allocated transfusion policy. The trial will recruit in 6 academic centers in the UK. Both feasibility and clinical outcome measures will be collected. Feasibility measures include recruitment rate, adherence to the transfusion policy, the difference in Hb, and RBC exposure between the restrictive and liberal transfusion policies and evidence of selection bias. Clinical outcomes include further bleeding, mortality, need for therapeutic endoscopy, need for surgery or radiological intervention to control bleeding, thromboembolic, and ischemic events, infections, transfusion reactions, and an assessment of quality of life at day 28 (EuroQol EQ-5D). Data will also be gathered to identify factors leading to contravention of the transfusion policy, and to enhance estimates of the intraclass correlation coefficient (ICC) to inform the sample size calculation for a phase III cluster randomized trial. The full trial protocol is available on the dedicated trial Web site: http://www.trigger.nhsbt.nhs.uk/.

### Randomization of Clusters

Widespread consultation was conducted amongst clinical stakeholders in each potential center to ensure a willingness to be randomized to either transfusion policy and agreement to implement the allocated policy on a hospital wide level. Centers will be randomized using permuted blocks without stratification or matching, in order to ensure an equal number of centers are assigned to each transfusion policy. Recruitment of patients will operate for 6 months in total in each center.

### Eligibility Criteria

Eligibility criteria relate both to those of the cluster and to the individual trial participants. Clusters (ie, hospitals) are eligible to take part if they meet the following criteria:•> 20 admissions with AUGIB per month•400 hospital beds•Availability of 24 hour endoscopy and on-site access to intensive care and surgical support•Willingness to be randomly allocated to a transfusion policy•Institutional agreement to transfuse all eligible new admissions with AUGIB in accordance with the randomized transfusion policy

Participants are eligible to take part in the study if:•They are aged ≥ 18 years presenting to hospital with AUGIB, defined as hematemesis or the passage of melena.

Participants are not eligible to take part in the study if:•The responsible clinician considers there is a need for immediate RBC transfusion prior to obtaining or regardless of the initial Hb result due to severity of bleeding.•They are an existing hospitalized patient who subsequently develops AUGIB.

No upper age limit has been set for patient level inclusion criteria. In the large UK audit of AUGIB, 28% of presentations were aged ≥ 80 years (1898/6750) and excluding this group would limit both the anticipated recruitment rate and generalizability of the trial findings. Whilst the assessment of severe bleeding is left to clinical judgment, additional pragmatic guidance include (but are not exclusive to) patients with features of hemodynamic shock (systolic BP < 100 mmHg and/or heart rate > 100 bpm) and receipt of RBCs within 2 hours of presentation, transfusion of emergency O-negative blood, or performance of the index endoscopy in an emergency clinical area due to severity of bleeding.

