#### Restrictive Transfusion Policy (RBCs Transfused When Hb ≤ 8 g/dL)

If the Hb value is recorded as ≤ 8.0 g/dL, RBCs should be transfused with the aim of keeping the Hb range between 8.1 and 10.0 g/dL. Further RBC transfusions should only be administered if the Hb value decreases to a value of 8.0g/dL or less.

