#### Liberal Transfusion Policy (RBCs Transfused When Hb ≤ 10 g/dL)

If the Hb value is recorded as ≤ 10.0 g/dL, RBCs should be transfused with the aim of keeping the Hb range between 10.1 and 12.0 g/dL. Further RBC transfusions should only be administered if the Hb value decreases to a value of 10.0 g/dL or less.

In both intervention arms the number of RBC units transfused and the timing of repeat Hb measurements will be decided by the caring clinician. Any transfusion(s) required as part of the policy should be administered within 24 hours of obtaining the Hb result.

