### Data Collection

#### Screening Log

A daily screening log of all patients admitted with AUGIB will record the total number of admissions, the number meeting eligibility criteria and eligible patients enrolled in each hospital. Anonymized, baseline clinical characteristics for each patient will be recorded.

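### The severe-bleeding exclusion guidance does not separate early RBCs given for severity from early RBCs given because the allocated Hb threshold was met, so exclusion can be influenced by the randomised policy

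*Protocol article*

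**What the plan says.** The formal patient-level exclusion (Eligibility Criteria) is a responsible clinician's judgment that there is a "need for immediate RBC transfusion prior to obtaining or regardless of the initial Hb result due to severity of bleeding". Guidance follows, introduced by "Whilst the assessment of severe bleeding is left to clinical judgment, additional pragmatic guidance include (but are not exclusive to". Its first item combines shock features with early transfusion: "systolic BP < 100 mmHg and/or heart rate > 100 bpm) and receipt of RBCs within 2 hours of presentation". Emergency O-negative blood and an index endoscopy done in an emergency area because of severity are the other items.

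The restrictive policy reads "If the Hb value is recorded as ≤ 8.0 g/dL, RBCs should be transfused". The liberal policy reads "If the Hb value is recorded as ≤ 10.0 g/dL, RBCs should be transfused". In both arms a policy transfusion "should be administered within 24 hours of obtaining the Hb result". Participant Screening and Selection applies the allocated policy from presentation to discharge.

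Outcomes lists three relevant measures:
- the proportion ineligible because of immediate transfusion need, for each arm;
- a between-arm comparison of age, shock, baseline Hb, Rockall and Blatchford scores and comorbidities in consented patients;
- a comparison of baseline Hb and the two scores between consented and non-consented patients.

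For the Screening Log, which covers all patients admitted with AUGIB, the article states: "Anonymized, baseline clinical characteristics for each patient will be recorded".

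**The concern.** Read literally, the formal criterion does not depend on a transfusion threshold, because it concerns RBCs given before or irrespective of the Hb result. The guidance item uses something else, namely treatment received within two hours, with no condition on its reason. That treatment comes after cluster allocation, and the allocation partly directs it.

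Take a patient with heart rate 105 bpm and Hb 9 g/dL. In a liberal centre prompt RBCs may be given because the threshold was met, and the patient then fits the guidance item. In a restrictive centre the same patient has no policy reason for RBCs and may never fit it.

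If staff use the item as a working rule, the enrolled populations can differ between arms in severity for a reason created by the intervention. Evidence of selection bias is a declared feasibility measure, and Sample Size says that large imbalances suggesting harm would influence a follow-on trial. The wording could also be carried into the phase III protocol.

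**Working it through.** **Step 1. The texts side by side**

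| Initial Hb, shocked patient | Liberal policy | Restrictive policy | Can policy alone produce RBCs within 2 hours? |
|---|---|---|---|
| 8.0 g/dL or less | RBCs | RBCs | In both arms |
| 8.1 to 10.0 g/dL | RBCs | No RBCs | In liberal centres only |
| Above 10.0 g/dL | No RBCs | No RBCs | In neither |

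The guidance item can respond differently to policy only in the middle row. The section on the 2007 audit calls this the range of genuine uncertainty: 51% were transfused and 49% were not, and the variability persisted after stratifying by hemodynamic abnormality. Patients in this row also meet the Hb limit of 12 g/dL for the primary clinical analysis. That set is a subset of those enrolled, so a distortion would be less diluted there.

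**Step 2. The plan's own figure**

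1062 × 0.80 = 849.6, stated as 849. It reproduces, rounded down.

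**Step 3. Illustrative number excluded**

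Inputs from the document:
- 1062 expected eligible patients;
- "62% of patients had no features of hemodynamic shock" in the audit cited in the introduction, so 38% had such features.

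Assumptions, none of them in the document:
- equal arms, 1062 / 2 = 531 each;
- a share *f* of shocked patients with Hb 8.1 to 10.0 of 10% to 30%, with Hb and shock independent;
- a probability *p*, by arm, of RBCs within 2 hours leading to exclusion.

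The figure 1062 is already described as eligible, so using it as the base is a simplification.

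Shocked per arm: 531 × 0.38 = 201.8. In the Hb band: 201.8 × 0.10 = 20.2, up to 201.8 × 0.30 = 60.5. Excess excluded from liberal centres = 201.8 × *f* × (*p* liberal − *p* restrictive).

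**Step 4. Illustrative effect on further bleeding**

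Assume a risk of 13% overall and 30% in the excluded patients, with no treatment effect. With *e* excluded, the arm rate = (531 × 0.13 − *e* × 0.30) / (531 − *e*).

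| *p* liberal / restrictive | Excess excluded from liberal (*f* = 10% to 30%) | Restrictive minus liberal rate, points |
|---|---|---|
| 25% / 25% | 0 | 0 |
| 10% / 5% | 1 to 3 | 0.03 to 0.10 |
| 25% / 10% | 3 to 9 | 0.10 to 0.30 |
| 50% / 10% | 8 to 24 | 0.26 to 0.83 |
| 50% / 0% | 10 to 30 | 0.33 to 1.03 |
| 20% / 30% | −2 to −6 | −0.07 to −0.21 |

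Example, 50% / 0% at *f* = 30%: *e* = 60.5 × 0.50 = 30.3 in liberal centres. The liberal rate is (69.03 − 9.08) / (531 − 30.3) = 11.97%, against 13.00% in restrictive centres.

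At 50% / 10% and *f* = 30%, the share of shocked patients left is 34.3% in liberal and 37.3% in restrictive centres.

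**Step 5. What the planned checks can show**

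The ineligible proportion by arm would show a difference in frequency, and the between-arm comparison of consented patients could show a difference in shock or Hb. Neither identifies the cause. Randomization of Clusters specifies no stratification or matching, so with three hospitals per arm a gap of a few points in shock could equally be hospital case-mix. The consented versus non-consented comparison appears to concern eligible patients, and would then not reach those ruled ineligible. No listed outcome describes the characteristics of the excluded group.

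**The case against.** The strongest reply is that the binding rule is the formal criterion. The two-hour item is guidance under clinical judgment, and it is joined to shock features by the word 'and', so RBC receipt alone is not a ground for exclusion. A patient transfused because Hb 9 g/dL met the liberal threshold was transfused on the Hb result and, read strictly, does not meet the formal criterion. Policy transfusions have 24 hours from the Hb result, so perhaps few fall within two hours of presentation. Clinicians may also transfuse off policy in either arm. All of this stands. It limits how often the problem would occur, but the two texts still point different ways for that patient.

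A reader might infer that shocked patients are in fact removed more often from liberal centres. The document does not support that, because it gives no data on early transfusion timing. The opposite is also possible: a restrictive-centre clinician who wants to transfuse at Hb 8.1 to 10.0 may declare immediate need, where a liberal-centre clinician can transfuse within policy.

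A reader might also infer that the selection-bias plan looks only at consented versus non-consented patients. That is wrong, since shock, baseline Hb and risk scores are also compared between arms.

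Finally, the illustrated bias is small. With about 425 enrolled per arm at an assumed 13%, the standard error of the difference is √(2 × 0.13 × 0.87 / 425) = 2.3 points before clustering, and Sample Size states that the trial is not powered on further bleeding or mortality. This stands as an argument on severity. It does not remove the route to bias, which a larger trial would inherit with less noise around it.

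**Conclusion.** The point holds as a moderate one. The guidance item lets treatment directed by the allocated policy count towards a post-allocation exclusion, and the policies differ on that treatment at Hb 8.1 to 10.0 g/dL. Exclusion can therefore be influenced by allocation. It is not shown that it will be, nor in which direction, although more exclusion in liberal centres is plausible.

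The size cannot be estimated from the document. The illustration runs from zero to about 1 percentage point in further bleeding, with a small reversal possible. It rests wholly on assumed values for the Hb share, early transfusion by arm and the risk in excluded patients. A rating of must-fix would not be justified in a feasibility trial on these figures. The planned checks offer partial detection, but not attribution to this cause or a description of who was excluded.

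**What to change.** 1. Reconcile the guidance with the formal criterion so that RBC receipt directed by the allocated policy does not by itself count as evidence for exclusion. Which patients are too severely ill to enrol remains a clinical decision.
2. Add one screening-log item: was the decision to transfuse made before or regardless of the Hb result (yes or no)?
3. From the screening log, compare Hb, shock and risk scores of enrolled patients with those of all AUGIB admissions, including those excluded for immediate transfusion, within each hospital. Then compare that difference between arms. Working within hospital removes much of the case-mix difference that clouds the planned between-arm comparison.

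The cost is one log item, one table and some redrafting, with possibly slightly more severe patients enrolled. The article reports that 75% of recruitment was complete when the external trial appeared, so the eligibility wording and the new log item mainly serve phase III. The comparison using characteristics already logged can still be done in TRIGGER.

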#### Clinician Discretion to Transfuse in Contravention of the Allocated Policy

All clinicians will have the discretion to transfuse, or not to transfuse, in contravention of the allocated policy for any patient admitted with AUGIB. Any clinician who deviates from the policy will be asked to provide the reason(s) for doing so on a Case Report Form. This is not designed to challenge the clinician’s judgment, but rather to identify patient subgroups, which may not be feasible to recruit into the planned phase III trial. Possible reasons for additional transfusions outside of the protocol could include periods of further bleeding or hemodynamic instability.

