### Outcomes

The study will collect a range of feasibility outcome measures and clinical outcome measures.

Feasibility outcome measures for each treatment arm include:•The proportion of eligible patients who provide consent.•The proportion of patients who are ineligible due to need for immediate transfusion.•Protocol adherence, which includes:1.Overall adherence: the proportion of Hb counts for each patient where no deviation occurred. This will be averaged across all patients.2.Adherence per Hb count: the overall proportion of Hb counts where no deviation occurred.3.Adherence per patient: the proportion of enrolled patients for whom no transfusion deviation occurred.•Selection bias: As the study is open-label, all clinicians will be aware of their hospital’s transfusion policy, resulting in the possibility of selection bias. The following outcomes will be compared between the 2 interventional arms in order to investigate this:oAge, shock, Hb at baseline, clinical Rockall score, Blatchford score, and the number of major comorbidities for consented patientsoThe difference in the baseline Hb, Rockall and Blatchford scores of consented vs. those not consented•The number of RBC units transfused•The proportion of patients receiving at least one RBC transfusion.•The mean Hb over the first 7 days after admission•The mean Hb over the entire study period (i.e. up to discharge/death/28 days)•The mean Hb on discharge (the last recorded Hb prior to discharge will be used)

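### The severe-bleeding guidance uses early RBC receipt as an exclusion marker, although RBC receipt is what the allocated policy sets, so eligibility can depend on the arm

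*Protocol article*

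**What the plan says.** The patient-level exclusion in Eligibility Criteria is a judged "need for immediate RBC transfusion prior to obtaining or regardless of the initial Hb result due to severity of bleeding". The same section then explains how severe bleeding may be recognised: "Whilst the assessment of severe bleeding is left to clinical judgment, additional pragmatic guidance include (but are not exclusive to") a short list. The first item combines "features of hemodynamic shock (systolic BP < 100 mmHg and/or heart rate > 100 bpm") with RBC receipt: "and receipt of RBCs within 2 hours of presentation". Because the two signs are joined by and/or, tachycardia alone supplies the shock part. Nothing says that the RBCs must have been given independently of the Hb result or of the policy.

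Under the Liberal Transfusion Policy, "If the Hb value is recorded as ≤ 10.0 g/dL, RBCs should be transfused". The restrictive trigger is 8.0 g/dL, so the policies differ for Hb 8.1-10.0. Participant Screening and Selection applies the policy from presentation to discharge. The policy section allows 24 hours from the Hb result for a policy transfusion.

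The section on clinician discretion treats transfusion outside the policy as a deviation whose reason is to be documented, and gives examples: "Possible reasons for additional transfusions outside of the protocol could include periods of further bleeding or hemodynamic instability". The feasibility outcomes, reported for each arm, include "The proportion of patients who are ineligible due to need for immediate transfusion", three adherence measures, and comparisons meant to reveal selection bias.

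**The concern.** An exclusion criterion in a cluster trial should not depend on anything the allocation can change. Receipt of RBCs is the thing allocated here, and the 2-hour window lies inside the period when the policy is in force. The guidance item is thus looser than the criterion it explains: it can be met by a transfusion that the Hb threshold triggered.

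Three feasibility measures are exposed. The proportion ineligible would mix bleeding severity with the effect of the policy. The selection-bias comparison between arms is made in consented patients, after any such exclusion has occurred. Adherence would lose from its denominator some early restrictive-arm deviations that the discretion section wants recorded. The Discussion says the feasibility end points will help decide whether clinicians adhere well enough to justify a phase III trial, so these distortions matter more than the effect on clinical outcomes.

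**Working it through.** **Logic check.** Take one patient with heart rate 105 and first Hb 9.0 g/dL.

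- Liberal centre: the policy calls for RBCs. If they are given within 2 hours of presentation, shock features and early RBC receipt are both present and the guidance item is met.
- Restrictive centre: the policy does not call for RBCs. The item is not met and the patient stays eligible, unless transfused off policy or caught by another item. If transfused off policy within 2 hours, the patient also meets the item and can be recorded as ineligible instead of as a deviation.

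**Inputs from the article.** Sample Size gives 1062 eligible patients and 80% consent: 1062 x 0.80 = 849.6, stated as 849, so the figure reproduces. Equal arms (an assumption) give 1062 / 2 = 531. The introduction reports that in the audit "62% of patients had no features of hemodynamic shock", hence 38% with them; I assume this also holds at Hb 8.1-10.0.

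**Inputs assumed, not in the article.** Share of patients in the 8.1-10.0 band, s = 10-25%. Extra share of shocked band patients transfused within 2 hours because of the liberal policy and then excluded, f = 10-50%.

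**Liberal-arm loss** = 531 x s x 0.38 x f.
- Low: 531 x 0.10 x 0.38 x 0.10 = 2.0 patients (0.38% of the arm).
- High: 531 x 0.25 x 0.38 x 0.50 = 25.2 patients (4.75% of the arm).

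The proportion ineligible would rise by about this percentage, or slightly less if the denominator is all admissions.

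**Restrictive-arm loss.** Assume 20-40% of band patients are transfused off policy and a quarter to a half of those are recorded as exclusions. The share of the band lost is 0.20 x 0.25 = 5% to 0.40 x 0.50 = 20%, or 531 x 0.10 x 0.05 = 2.7 to 531 x 0.25 x 0.20 = 26.6 patients. The liberal share of the band lost, with f = 20-50%, is 0.38 x f = 7.6-19%. The two ranges overlap almost fully.

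**Whole-arm outcome shift, if only one arm lost patients.** With x the share of the arm removed, remaining shock prevalence is p' = (0.38 - x)/(1 - x). Assume further-bleeding risk of 20-25% with shock and 10% without, a gap of 10-15 points.

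| s, f | x | p' | Shift = (0.38 - p') x gap |
|---|---|---|---|
| 10%, 10% (2 patients) | 0.0038 | 37.8% | 0.02-0.04 points |
| 15%, 20% (6 patients) | 0.0114 | 37.3% | 0.07-0.11 points |
| 25%, 50% (25 patients) | 0.0475 | 34.9% | 0.31-0.46 points |

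For 6 to 25 patients the shift is therefore roughly 0.1-0.5 points. Losses of similar patients in both arms would partly cancel.

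**Adherence per patient, restrictive arm.** With d the off-policy share and c the share of those recorded as exclusions, measured adherence is (1 - d)/(1 - d x c). Within the band, 80% becomes 0.80/0.95 = 84.2% or 0.80/0.90 = 88.9%; 60% becomes 0.60/0.90 = 66.7% or 0.60/0.80 = 75.0%. Over the whole arm, counting only band deviations, s = 15%, d = 20%, c = 25% gives 97.0% rising to 0.97/0.9925 = 97.7%; s = 25%, d = 40%, c = 50% gives 90.0% rising to 0.90/0.95 = 94.7%. These are upper readings, because the item reaches only shocked patients transfused within 2 hours, whereas deviations can occur at any time.

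**The case against.** The strongest reply is that the parent criterion already settles the worked example. A patient transfused because the Hb came back at 9.0 was not transfused before or regardless of that result, so on a strict reading is not excluded. The guidance is non-exhaustive, needs shock features as well, and defers to clinical judgment. With 24 hours allowed for a policy transfusion, RBCs within 2 hours in a shocked patient may well signal real urgency. This stands in part: it makes exclusion possible, not automatic. It does not remove the problem. Clinicians know the allocation, admission lists are screened daily, and the Discussion says most patients arrive out of hours. Eligibility may thus often be judged with an early transfusion already on the chart.

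A second reply is that the trial monitors this. Ineligibility for immediate transfusion is reported by arm, and the screening log covers all AUGIB admissions with baseline characteristics. That helps detection, but it neither prevents the exclusion nor separates policy from severity within the proportion ineligible. The full protocol, not shown, may also give more operational detail.

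A reader might infer that only the liberal arm loses high-risk patients, so that liberal outcomes look better. The article does not support this: the restrictive arm can lose patients from the same band, and the net direction is not established. A reader might also set the band-only shift (0.5-2.2 points on the assumed risks, with f = 20-50%) against the 6-point difference in the external single-centre trial (10% v 16%). That comparison is mismatched, because one figure covers a part of one arm and the other a whole trial.

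**Conclusion.** The point holds in a limited form. The guidance item is looser than its parent criterion and lets eligibility depend on the allocated policy in both arms, with neither automatic exclusion nor a known direction of bias. The sizes rest on the assumed band share, early-transfusion share, recording share and risks. They also rest on equal arms, and on applying an audit shock rate, from patients with no such exclusion stated, to a count of 1062 that is already net of exclusions. On that footing the effect on clinical outcomes is small, in a trial not powered on further bleeding or mortality. The consequence worth acting on is that the proportion ineligible (up to about 5 points), the selection-bias comparison and adherence cannot be read cleanly by arm.

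**What to change.** Reconcile the guidance item with its parent criterion: it should count only RBCs given before, or regardless of, the initial Hb result because of bleeding severity, and not RBCs triggered by the allocated Hb threshold. Both halves of the criterion should stay; counting pre-result requests alone would drop the second half. The change concerns how patients are classified, and clinicians' discretion to transfuse is untouched.

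Record on the screening log the RBC request time, the Hb result time and the reason for exclusion. Report by arm the exclusions made through this item with a first Hb of 8.1-10.0 g/dL, and show the comparison of proportion ineligible a second time for pre-result exclusions alone. Since the article says 75% of recruitment was complete when the external trial was published, the by-arm report from the log is the most useful step for exclusions already made, as far as the log holds the data. The reworded item can carry into phase III.

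The cost is one line of guidance, two times and a reason on the log. Some judgment in deciding what was given regardless of the Hb will remain.
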